## 7.0 RISK MANAGEMENT

### 7.1 Pregnancy and breastfeeding

Health Canada has not approved the use of HCQ for women who are currently pregnant, planning to get pregnant, or who are breastfeeding. Women meeting these criteria at the screening will be ineligible to enroll. Further, women of childbearing potential (WOCP) will have a screening urine pregnancy test and only those with negative tests will be enrolled. Urine pregnancy tests will be done on WOCP at each study visit. Women who become pregnant during the study will be asked to inform the study coordinator and to stop their study drug and will discuss follow-up with the participant. All WOCP at the

beginning of the study will agree to the use of a contraceptive method. Pregnancy is not an adverse event; however, any complication related to pregnancy should be considered an adverse event.

## 7.2 Protection of Study Personnel from COVID-19

COVID-19 is believed to be transmitted from person-to-person through respiratory droplets and via fomites. While the greatest risk of transmission is believed to occur in the context of respiratory symptoms, transmission from asymptomatic and minimally symptomatic individuals may occur. For these reasons, several measures will be taken to minimize the risk of transmission to study personnel and participants.

First, the group information session for consent will be conducted remotely. Weekly online questionnaires will collect the majority of data required from participants, further reducing person-to-person contact in the monthly interview. For study visits conducted in person, if the participant does not have symptoms of COVID-19 (see Questionnaire Content document), universal precautions will be undertaken for the interview and phlebotomy. If the participant fails the symptom screen, a surgical mask should be placed on the participant and full droplet precautions will be followed by study staff (i.e. surgical mask, eye protection, gown, glove). Any study staff person who develops symptoms potentially suggestive of COVID-19 should immediately be assessed by the site occupational health department and relieved of study duties until deemed safe to return to work.

## 7.3 Drug Safety and Monitoring Board

Risk minimization, management, and assessment procedures have been implemented in the study to minimize and assess potential risks to participants who participate in this clinical study with HCQ. Components include: (1) specific study entry and exclusion criteria to ensure that participants who have underlying condition that potentially increase their risk for an adverse outcome are excluded; (2) overview surveillance by an independent Data Safety Monitoring Board (DSMB); (3) follow-up (monthly) for safety monitoring purposes at in-person study visits.

The DSMB will include infectious diseases and public health specialists, at least one biostatistician, and researchers with an understanding of emerging infections and clinical trials, not involved in the trial. The DSMB will meet after half the expected number of infections have occurred in the trial. The purpose of the DSMB will be to review safety concerns, conduct and review the interim analysis and review external data that may have bearing on the design of or decision to continue the trial. The committee will meet at

further 1 month intervals and provide feedback to the principal investigator; however, the responsibility for the final decision regarding a DSMB-recommended course of action will rest with the principal investigators.

In the event that the outbreak has ended at one or more study sites and the study has not yet been completed, the study should be paused. Efficacy data from the trial must not be prematurely released. In this instance, the DSMB should conduct an interim analysis of the study data to make recommendations whether the study should continue or stop for efficacy, futility or safety. As per World Health Organization policies on data-sharing in a Public Health Emergency, clinical trial outcome data will be shared at the earliest possible opportunity.

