### 11.2 Sample Size Considerations/Justification

The 3-month risk of infection in healthcare workers not treated with prophylaxis was assumed to be 10%. This corresponds to a hazard of 0.035 infections per month under the assumption of exponentially-distributed time to infection. Reducing 3-month risk to ~6% was judged to be both feasible and clinically important; this reduction corresponds to a hazard ratio of 0.588. With a one-sided type I error rate of 5%, to have 80% power, to detect this hazard ratio, a total of 92 events are needed. Using the event rates above and exactly 3 months + 14 days planned follow-up for each participant, a total of 988 participants need to be randomized. These calculations account for the single interim analysis described below.

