### 11.3.3 Interim Analysis

One interim analysis of the primary outcome is planned when half the expected number of events (46/92) has occurred. The table below shows the properties of this design. At the first interim analysis, a Z-statistic ( $-\log(\text{HR})/(\text{Standard Error})$ ) larger than 2.67 will be taken as evidence of efficacy; this is the same as checking whether the one-sided p-value is  $< 0.0038$ . If the true hazard ratio is 0.588 (as in the sample size calculation), there is a 19% chance of stopping for efficacy at this interim analysis. The trial may stop for futility (with the recommendation coming from the DSMC, as this is a non-binding futility boundary) if the Z-statistic is less than -0.01, which corresponds to the one-sided p-value being  $> 0.51$ . If the true HR is 1.0, there is a 49% chance that the interim analysis will cross this futility boundary. If the trial does not stop for futility or efficacy, the final analysis will take place at the earlier of the date that all participants have reached the end of the 104-day randomized or when 92 events have occurred. This final analysis will declare superiority of HCQ over placebo if the Z-statistic is  $> 1.65$  (or the one-sided p-value is  $< 0.049$ ). With 92 total events, power is 80% against  $\text{HR}=0.588$  and type I error is 5% across the whole trial. One-sided testing is justified here to increase power, as there is no interest in concluding that HCQ is inferior to placebo. A finding other than HCQ being superior will lead to the same decision not to use it.

| Analysis   | Value                        | Efficacy | Futility |
|------------|------------------------------|----------|----------|
| IA 1: 50%  | Z                            | 2.6700   | -0.0142  |
| N: 988     | p (1-sided)                  | 0.0038   | 0.5057   |
| Events: 46 | HR at bound                  | 0.4542   | 1.0042   |
| Month: 1.7 | P(Cross) if $\text{HR}=1$    | 0.0038   | 0.4943   |
|            | P(Cross) if $\text{HR}=0.59$ | 0.1864   | 0.0365   |
| Final      | Z                            | 1.6549   | 1.6549   |
| N: 988     | p (1-sided)                  | 0.0490   | 0.0490   |
| Events: 92 | HR at bound                  | 0.7076   | 0.7076   |
| Month: 3.5 | P(Cross) if $\text{HR}=1$    | 0.0489   | 0.9511   |
|            | P(Cross) if $\text{HR}=0.59$ | 0.8000   | 0.2000   |

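### Section 7.3 allows an efficacy look that the 5% error claim in 11.3.3 does not cover, so if the outbreak trigger occurs the 5% is not guaranteed

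*Protocol*

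**What the plan says.** Protocol section 11.3.3 sets out the group-sequential design: "One interim analysis of the primary outcome is planned when half the expected number of events (46/92) has occurred". Efficacy is declared at that look if Z exceeds 2.67 (one-sided p < 0.0038). There is a non-binding futility bound at Z = -0.0142. The final analysis requires Z > 1.65 (1.6549 in the table, p < 0.049). The section then states that "type I error is 5% across the whole trial". Section 11.2 says of the sample size: "These calculations account for the single interim analysis described below". The synopsis and section 2.1 also describe one interim.

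Section 7.3 first has the DSMB meet at half the expected infections. In a separate paragraph it turns to the case where the outbreak is over at one or more sites while the trial is unfinished. The study is then to be paused, and "the DSMB should conduct an interim analysis of the study data to make recommendations whether the study should continue or stop for efficacy", with futility and safety as the other grounds. No information fraction, critical value or change to the final bound is given there, and section 11.3.3 does not mention this look.

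**The concern.** The protocol fixes the number of efficacy looks, their numerical bounds and the overall error in one section, then orders an efficacy look outside that scheme in another. The trigger is broad: one site of five is enough, at any event count, and several sites could trigger it in turn.

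A chance to claim efficacy that is not paid for out of the 5% raises the false-positive rate unless the other bounds are tightened. The threshold would also be chosen at the time of the look, when the DSMB can see unblinded data. A boundary fixed in advance exists to prevent that. At stake is the error rate of the primary conclusion, in a trial that already tests one-sided at 5%.

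**Working it through.** **Inputs from the protocol.** One-sided alpha 5%, 92 events and hazard ratio 0.588 (section 11.2). Interim at information fraction t = 46/92 = 0.5 with Z > 2.67, futility Z < -0.0142 and non-binding, final Z > 1.6549 (section 11.3.3).

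**Assumed, because section 7.3 gives neither.** The extra look falls at t = 0.25 to 0.80. Its critical value is 2.67 (the protocol's only interim efficacy bound), 1.96 (nominal 0.025) or 1.645 (nominal 0.05).

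**Method.** Under the null hypothesis the Z-statistics at fractions s < t are jointly normal with mean 0, variance 1 and correlation sqrt(s/t). Overall error = 1 - P(Z stays at or below its bound at every look).

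**Step 1: reproduce the stated figure.**
- P(Z at 0.5 > 2.67) = 0.0038.
- P(no crossing at 0.5, then Z at 1 > 1.6549) = 0.0462.
- Total = 0.0038 + 0.0462 = 0.0500.
- If futility stopping is always obeyed, the total is 0.0489, as tabled.
- Power, with drift sqrt(92/4) × (-ln 0.588) = 2.547, is 0.81 against the stated 0.80.

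The 5% claim is right for the design as tabled. With futility non-binding, no alpha is left over.

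**Step 2: add one efficacy look and leave the planned bounds unchanged (futility non-binding).**

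| Critical Z at extra look | t = 0.25 | t = 0.60 | t = 0.75 | t = 0.80 |
|---|---|---|---|---|
| 2.67 | 5.2% | 5.0% | 5.0% | 5.0% |
| 1.96 | 6.7% | 5.9% | 5.6% | 5.5% |
| 1.645 | 8.7% | 7.6% | 7.0% | 6.8% |

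Two extra looks, at t = 0.65 and 0.80, give 8.2% at Z > 1.6549, or 5.03% at Z > 2.67.

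**Step 3: read 7.3 as moving the single interim rather than adding one.** With the final bound unchanged:
- Z > 2.67: 5.12% at t = 0.25, 5.09% at 0.30, 5.04% at 0.40.
- Z > 1.96: 6.7% at t = 0.25 to 5.6% at 0.75.
- Z > 1.645: 8.7% at t = 0.25 to 7.0% at 0.75.

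**Step 4: check that spending restores 5%.** The protocol names no spending function. A Hwang-Shih-DeCani function with gamma = -5, alpha(t) = 0.05 × (e^(5t) - 1)/(e^5 - 1), gives:
- alpha(0.25) = 0.05 × 2.490/147.41 = 0.0008
- alpha(0.50) = 0.05 × 11.18/147.41 = 0.0038, which matches the table
- alpha(0.75) = 0.05 × 41.52/147.41 = 0.0141

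With looks at 0.50, 0.75 and 1, the bounds become Z = 2.670, 2.237 and 1.673. With looks at 0.25, 0.50 and 1, they become 3.140, 2.724 and 1.657. Total error is 0.0500 in both cases, and power is about 81% with futility stopping ignored.

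**The case against.** **The 0.0038 threshold would be reused.** It is the only interim efficacy threshold in the protocol, and section 7.3 puts a biostatistician on the DSMB. On that reading the excess is at most about 0.2 percentage points. If futility stopping is also obeyed, the error is 5.09% at t = 0.25, 4.99% at 0.40 and 4.92% at 0.60. This stands, and it is why the nominal thresholds are only a worst case. It does not settle the matter, because section 11.3.3 ties that bound to the 46-event look and nothing carries it into section 7.3.

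**Section 7.3 may only bring the single interim forward.** This is possible before 46 events, but the bound at the new fraction is still undefined (step 3). It cannot apply once the planned look has been taken.

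**An ended outbreak may leave the trial short of 92 events.** Section 11.3.3 permits a final analysis once everyone has completed 104 days. If the 46-event look is never reached and the extra look falls at 70% to 95% of the final information with Z > 2.67, the error is 4.93% to 4.90%. This also stands, but only with that threshold.

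**Boundary detail belongs in a SAP or DSMB charter.** Neither is shown, so the absence of a boundary in section 7.3 alone would not be a finding. What remains is a conflict between two statements in the protocol: a single interim with 5% across the whole trial, and an order for another efficacy look.

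**A stronger reading to avoid.** A reader might infer that the 5% claim is simply false, or that the trial runs at nearly 9%. The documents support neither. The claim is correct if the trigger does not occur, and the larger figures rest on thresholds the protocol never proposes.

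**Conclusion.** The inconsistency is real but conditional. Section 7.3 provides for an efficacy look that sections 11.2 and 11.3.3 do not count, and the planned looks use all of the 5% when futility is non-binding. If the outbreak trigger occurs and efficacy is assessed, 5% is no longer guaranteed.

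For one extra look at 25% to 80% of information, with the planned bounds unchanged and 92 events reached, the error is about 5.0% to 5.2% if Z > 2.67 is reused. It is 5.5% to 6.7% at nominal 0.025 and 6.8% to 8.7% at nominal 0.05. The first range is negligible. The others are a worst case under assumed thresholds. The protocol should be amended because its text does not determine which of these applies, and the correction is cheap.

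**What to change.** Make one of two changes, worded the same way in sections 7.3 and 11.3.3.

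1. State that any efficacy look, planned or triggered, uses a named alpha-spending function evaluated at observed events/92, and that the final Z is recomputed from the looks actually taken. Hwang-Shih-DeCani with gamma = -5 reproduces the tabled 0.0038 at 50%. It is inferred from that one figure, so the sponsor should confirm what was used. Under it, an extra look at 75% would need Z of about 2.24, and the final bound would move from 1.65 to about 1.67.
2. Or limit the outbreak-ended look to safety and non-binding futility. The present bounds and the 5% statement then stand as written.

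Either change is about one paragraph, with no added participants or visits. The first sets a stricter bar at the unplanned look than a nominal test would, and a slightly higher final bound. The second gives up the chance to stop early for efficacy when the outbreak ends.

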#### 7.4 Informing Participants of Amendments After Enrollment

Several participants will have started participation in this study prior to the amendment of May 13th, 2020. Participants already enrolled will be called by their study coordinator to review the amendments and they will be invited for their 1 month study visit at the earliest possibility in the visit window (21 days-30 days) to review and sign the addendum form and then complete additional procedures.

## 8.0 CLINICAL AND LABORATORY EVALUATIONS

### 8.1 Clinical Evaluations

All in-person study visits will begin with a COVID-19 symptom screen (see Questionnaire Content document). If the participant fails the symptom screen, a surgical mask should be placed on the participant and full droplet/contact precautions will be followed by study staff (i.e. surgical mask, eye protection, gown, glove). Any participant screening positive for symptoms of COVID-19 will then be directed to the most appropriate place for a confirmatory COVID-19 test (within the department or occupational health as per site institutional guidelines).

For all COVID-19 screen negative participants, study staff will conduct brief interviews to document medical history (baseline comorbidities and medications at day 1 and then new comorbidities, medications, adverse events and side effects at day 30,60,90,120). No physical examinations are required in this study. All WOCs will have a screening urine test at Day 1, 30, 60 and 90. All participants will have a review of a baseline QTc interval measure at Day 1 and a repeat QTc measure at Day 30, 60, 90 and 120. Participants

with a baseline QTc between 430-450 ms will be referred for a repeat QTc measure within 72 hours of commencing study drug.

All side effects will be documented by the study coordinator. The study coordinator has experience in implementing clinical trials of investigational agents and collecting and documenting AEs/SAEs. It is the study physician who will assess severity and relationship to study drug. If the side effect is attributed to the study tablet and has an impact on the participant's functional status (ex. ability to work) or general state of well being, the Study Physician will be responsible for further follow up. Ultimately, the participant will be supported in any decision they make regarding the continuation of study tablets.

If a participant becomes COVID-19 positive at any time in the study, all further in-person clinical evaluations will occur remotely (via telephone call) in light of necessary self-isolation and reducing risk to study staff. They will not have further respiratory specimens or phlebotomy collected while they have symptomatic COVID-19.

Further clinical data will be obtained in weekly emails sent to participants to fill in a short online form including self-report of COVID-19 symptoms/testing/outcomes/time off work, and adherence. Measures of psychological distress will be sent via email in a similar fashion at 1, 60 and 120 days.

Data will be recorded onto standardized electronic forms using the Research Electronic Data Capture system (REDCap) housed on secure servers at the AHRC at St. Michael's Hospital.

## 8.2 Laboratory Evaluations and Specimen Collection

### 8.2.1 Overview of Biologic Sample Collection

- Viral detection samples will be self-collected by participants with instructions from study staff (see Section 8.2.1 and 8.2.2)
- Venous blood samples will be collected by study research coordinators. All research coordinators have been trained and are experienced with venipuncture. They have all been trained and will be retrained on PPE donning and doffing as part of study start-up training. This will be kept as part of ISF training log.
- There will be strict observance of IPAC guidelines on interactions with asymptomatic participants (current recommendation: routine precautions) and symptomatic participants (current recommendation: droplet/contact precautions) as outlined in Section 7.2.

- Urine samples will be self-collected by female participants of child bearing age into sterile urine containers for pregnancy testing.

#### 8.2.2 Microbiologic testing for SARS-CoV-2

Specimens for viral RNA testing will be collected at each study visit. Participants will be instructed on self-collection of nasopharyngeal, oropharyngeal, nasal and/or oral swabs or saliva for RT-PCR testing and specimens will undergo biobanking if not tested in real-time for future analysis. The final collection method to be used in the study will be made based on the availability of the collection kits for the study. If oropharyngeal/nasal swabs are not available, saliva will be collected. Self-collection of swabs has been validated in multiple other settings and will allow for reduced exposure to study staff. These tests are for the purposes of investigating asymptomatic COVID-19 infection (as per the protocol any symptomatic participants will be tested through the most appropriate institutional methods – ie. occupational health or the ED). Specimens will be extracted using an automated system (easyMAG) and real-time PCR conducted using primers and probes against genes encoding the RNA-dependent RNA polymerase (RdRp) and the envelope (E) protein of COVID-19. Quantitation against a standard curve will be calculated in RNA copies/microliter.

#### 8.2.3 SARS-CoV-2 Serology

Methods for serologic testing of COVID-19 are still in development worldwide at the time of writing, but are rapidly emerging. Participants will undergo venipuncture at baseline, and monthly until and including the 120 day visit and samples processed into plasma for frozen storage by [name] laboratory (co-PI). Frozen samples will be batch-tested in the laboratory of Co-I [name] at the conclusion of the study when methods are finalized.

#### 8.2.4 Plaque reduction assay

Participants who become infected will have had venous samples drawn and plasma previously drawn at scheduled monthly visits, collected by research staff and brought according to an approved SOP to the [name] laboratory. It will be frozen at -80C and later tested for SARS-CoV-2 viral plaque reduction assay to determine circulating antiviral activity in infected participants. These studies will be in a BSL3 facility approved for these studies (conducted by [name]). UHN and U of T Biosafety have approved sample handling for this study.

#### 8.2.5 Biomarkers of disease severity

Plasma samples (minimum required volume of 250 µL) collected from participants at study enrolment and scheduled study visits will be processed via a custom multiplex Luminex®-based assays or ELISA to quantify plasma levels of markers of host response

to infection including inflammation, gut-leak, and endothelial activation in the laboratory of [name]. Analytes include Angiopoietin (Ang)-1, Ang-2, soluble Tyrosine kinase with immunoglobuline-like and EGF-like domains (sTIE)1, sTIE2, Vascular Endothelial Growth Factor (VEGF), soluble VEGF-receptor1, soluble Endoglin (sEng), soluble Intercellular Adhesion Molecule (sICAM), soluble Tumour Necrosis Factor (sTNF) receptor 2 (sTNFR2), C5a, Chitinase-3-like protein 1 (CHI3L1), C-reactive protein (CRP), Interleukin (IL)-18 binding protein (IL-18BP), IL-6, Zo-1, zonulin, Lipopolysaccharide-binding protein (LBP) ,and Intestinal fatty acid binding protein (I-fabp). Proteins were selected based on evidence of a critical role of in inflammatory pathways that mediate disease severity.

UHN and U of T Biosafety have approved sample handling and the testing procedure for this study.

### 8.3 Stored Research Specimens and Plans for Possible Future Testing

Any respiratory, serum and/or plasma specimens collected from participants but not analyzed in real-time will be stored in a biobank for potential future testing related to respiratory pathogen diagnostics and inflammatory biomarkers. Consent will be obtained for the storage of these samples for future testing.

### 8.4 Questionnaires and/or Scales

Questionnaires will be electronically administered weekly through REDCap, which will be emailed to participants directly (consent will be granted for email contact). Those lacking email/internet access may complete questionnaires on paper and/or by interview by study staff (may be done remotely). Then, weekly, all participants will be asked to complete self-report of COVID-19 symptoms/testing/outcomes/time off work, and adherence. For participants with confirmed COVID-19, questions will also include symptom duration, hospitalization, respiratory support and time ineligible/unable to work due to COVID-19. An email reminder will be sent for each questionnaire at day three of each weekly cycle and repeated twice.

The same online system will be used to measure study drug adherence, using a modified version of the ACTG adherence scale. This scale was developed by the AIDS Clinical Trials Group to assess adherence to antiretroviral therapy. This scale is brief, easy to use, and was rigorously developed, with high internal consistency and construct validity among adults taking antiretroviral therapy for HIV. Results will be scored according to the included items from this scale.

Finally, at day 1, 60 and 120, participants will also be asked to complete the K10, a short ten-item scale to measure non-specific psychological distress. A standard cutoff score of  $\geq 16$  will be used to define short-term psychological distress.

